### Examples of outcome definition

Pregnancy and neonatal outcomes will be retrieved from the SPR and SNQ, either registered as tick boxes, actual measures or International Classification of Diseases 10th revision (ICD-10) codes: Pre-eclampsia (ICD-10 O14), gestational age at birth, preterm delivery (with subanalyses for early, moderate, late preterm delivery as well as spontaneous vs iatrogenic preterm delivery), birth weight, small for gestational age, birth asphyxia, and perinatal death.Thromboembolic event diagnosis will be retrieved from the SPR and the National Patient Register (ICD-10 I82, I26).Vertical transmission as defined by Shah *et al.*
38
Child development and health: Developmental delays or potential delays as measured by ASQ up to 4 years of age. Neurological disorders diagnosed during the first 4 years of life (composite) retrieved from the National Patient Register; Any mental or behavioural disorder (ICD-10 F00–F99), impaired vision (H54), impaired hearing (H90, H91), cerebral palsy and other paralytic syndromes (G80–G83).Presence of antibodies in umbilical cord blood (IgG, IgM) and breast milk (IgG, IgM, IgA).

Subanalyses will be performed to study the impact of country of birth, socioeconomic status or underlying disease in the mother (eg, obesity, hypertension, diabetes, asthma).

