Box 1Swedish national health and quality registers that will be linked to the COVID-19 in Pregnancy and Early Childhood dataset (COPE dataset)The Swedish Pregnancy RegisterA certified national quality register initiated by the Swedish healthcare regions that combines prospectively collected data from the Swedish Maternal Health Care Register, the Swedish National Quality Register for Prenatal Diagnosis and data from electronic, standardised, prenatal delivery and neonatal records. The register includes more than 95% of all deliveries in Sweden and covers pregnancies from the first antenatal care visit until the follow-up visit at 8–12 weeks post partum. It contains information on maternal characteristics, medical and reproductive history, pregnancy examinations, delivery outcomes and follow-up^41^ (http://www.graviditetsregistret.se/).Examples of variables that will be extracted: pregnancy loss after first visit to antenatal care, body mass index at booking visit, weight gain during pregnancy, gestational age at delivery, mode of delivery, postpartum blood loss, birth weight, Apgar score and pregnancy complications such as gestational hypertension, pre-eclampsia and gestational diabetes.The Swedish Neonatal Quality RegisterA national quality register for neonatal care. All neonatal departments in Sweden report standardised data on admitted infants including basic information about pregnancy and childbirth, as well as the condition, treatment and diagnoses of the infant according to the Swedish version of International Classification of Diseases 10th revision (ICD-10), as well as information from follow-up visits. During the COVID-19 pandemic, all children born to mothers testing positive for SARS-CoV-2 are registered in the Swedish Neonatal Quality Register^42^ (www.snq.se).Examples of variables that will be extracted: admission to neonatal intensive care unit (NICU) or neonatal special care (NSC), duration of NICU/NSC stay, mechanical ventilation, asphyxia related complications, hypothermia treatment.The Swedish Intensive Care RegisterA Swedish quality register on intensive care. Data regarding severity of disease and interventions will be retrieved from Swedish Intensive Care Register for women requiring care at an ICU (http://www.icuregswe.org/).Examples of variables that will be obtained: duration of stay, mechanical ventilation, extracorporeal membrane oxygenation.The National Patient RegisterA mandatory health register including diagnoses on hospital admissions and outpatient visits in specialist care. Information will be retrieved on ICD-10 diagnoses and interventions for women during pregnancy and the postpartum period, chronic or previous disease in the mother as well long-term follow-up of their children^43^ (https://www.socialstyrelsen.se/statistik-och-data/register/alla-register/patientregistret/).Examples of variables that will be extracted: ICD-10 diagnosis of COVID-19 or diagnosis of thromboembolism for the mother during pregnancy as well as 3 months postpartum, diagnosis of neuropsychiatric disease during childhood.The National Cause of Death RegisterThe national cause of death register is based on the obligatory death certificates that need to be signed by a medical doctor confirming the cause of death in the deceased. Both the date and cause of death are registered.(https://www.socialstyrelsen.se/statistik-och-data/register/alla-register/dodsorsaksregistret/)Examples of variables that will be extracted: Time point and cause of death for mothers in the study population until 42 days after delivery, time point and cause of neonatal deaths.The Swedish Prescribed Drug RegisterA mandatory register holding data on all prescribed substances, Anatomical Therapeutic Chemical classification-code and date of purchase, for all dispensed drugs in the outpatient population.^44^

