### Sample size calculations

This is an exploratory study where the initial sample size for recruitment is set to 200 women in the COVID-19 group and 1000 in the screening group (with an additional 10%–15% with assumed positive tests in the screening group thus more than 300 COVID-19 cases). Sample size has been calculated with 80% power and a significance level of <0.05 based on the assumptions shown in table 3. As outcomes are retrieved from population-based registers, there will be close to complete follow-up.

**Table 3 T3:** Assumptions for power calculation

Outcome	Prevalence in screening group	Prevalence in COVID-19 group	Sample size screening group	Sample size COVID-19 group
Pre-eclampsia	6%	12%	511	256
Thrombosis	0.13%	2%	613	306
Small for gestational age (below 10th percentile)	10%	20%	199	199
Preterm delivery	6%	12%	511	256
Neurological and/or neurodevelopmental disorders	1%	4%	581	290

The percentage of women with vertical transmission secondary to active COVID-19 at the time of delivery (14 days before to 2 days after delivery) will be calculated.

Depending on the prevalence of malformations, the presence and type of malformations in case of infection during early pregnancy will be presented in a purely descriptive manner.

The presence of antibodies in umbilical cord blood and breast milk will be studied in relation to gestational week of infection, severity of infection and maternal serum antibody levels. Antibody levels will be followed over time.

Due to the unprecedented nature of the pandemic, it is difficult to perform formal power calculation with regard to parent health and mental well-being.

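### The ICD-10 list given for thromboembolic events (I82, I26) omits the pregnancy, puerperium and leg-vein categories, although the outcome is sought in pregnancy and 3 months post partum and is powered on about 7 events

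*Protocol article*

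**What the plan says.** Under Examples of outcome definition, the article states: "Thromboembolic event diagnosis will be retrieved from the SPR and the National Patient Register (ICD-10 I82, I26"). These are the only codes it gives for the outcome; O22, O87, O88 and I80 appear nowhere.

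Box 1, under the National Patient Register, sets the window. The variable to be extracted is "diagnosis of thromboembolism for the mother during pregnancy as well as 3 months postpartum".

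Table 3 (Sample size calculations) includes the outcome as the row "Thrombosis 0.13% 2% 613 306": prevalence in the screening and COVID-19 groups, then the two group sizes. The text adds: "Sample size has been calculated with 80% power and a significance level of <0.05". It gives no source for the two prevalences and no definition behind them.

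Two statements affect how strictly the code list should be read. The section is headed "Examples of outcome definition", and its item on pregnancy and neonatal outcomes says these are "either registered as tick boxes, actual measures or International Classification of Diseases 10th revision (ICD-10) codes". That same item uses an obstetric-chapter code, O14, for pre-eclampsia.

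**The concern.** The outcome lies, by its own window, in pregnancy and the first 3 months after delivery. ICD-10 has obstetric categories for these events: O22 for venous complications in pregnancy (O22.3 deep, O22.5 cerebral), O87 for the puerperium (O87.1 deep, O87.3 cerebral) and O88.2 for obstetric blood-clot embolism. Outside that chapter, deep-vein thrombosis of the leg is I80.1–I80.3, while I82 holds other venous embolism and thrombosis. The listed pair therefore leaves out the categories where correctly coded events in this population belong. This follows from the structure of the classification the protocol itself uses and can be checked in its Swedish version.

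A register query run as written would count a woman with such a code as event-free. Table 3 expects about 7 events in total, so a few missed cases can decide the comparison. Recruiting more women would not recover events that the query never looks for.

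**Working it through.** **Inputs from the documents.** Prevalence p1 = 0.13% (screening) and p2 = 2% (COVID-19); n1 = 613, n2 = 306; 80% power; alpha 0.05 (Table 3 and text). Planned recruitment is 1000 screening and 200 COVID-19 women, with 10–15% of the screening group assumed to test positive (Sample size calculations). Categorical outcomes are compared by chi-square or Fisher's exact test (General statistical methodology).

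**Assumption.** The share s of true events that I82 and I26 capture is not in the documents. It is taken as 75%, 50% or 25%, equal in both groups.

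**Step 1: reproduce Table 3.** Two-sided, pooled variance, no continuity correction:

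power = Φ{ [|p2 − p1| − 1.96·√(p̄(1 − p̄)(1/n1 + 1/n2))] / √(p1(1 − p1)/n1 + p2(1 − p2)/n2) }

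- Expected events: 613 × 0.0013 = 0.80 and 306 × 0.02 = 6.12.
- p̄ = 6.92/919 = 0.00753; null standard error 0.00605; alternative standard error 0.00814.
- (0.0187 − 1.96 × 0.00605)/0.00814 = 0.84, so power is 80.0%.

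The stated 613/306 reproduces, so the sample-size arithmetic is not at fault.

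**Step 2: planned group sizes.** 10% of 1000 moved gives 900 and 300; 15% moved gives 850 and 350.

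**Step 3: multiply both prevalences by s and repeat.**

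| Capture s | Expected events at 613/306 | Formula, 613/306 | Exact Fisher, 613/306 | Formula, 900/300 | Formula, 850/350 |
|---|---|---|---|---|---|
| 100% | 0.80 + 6.12 | 80.0% | 86.0% | 85.5% | 86.9% |
| 75% | 0.60 + 4.59 | 70.2% | 73.5% | 77.2% | 78.5% |
| 50% | 0.40 + 3.06 | 56.5% | 50.6% | 64.9% | 65.4% |
| 25% | 0.20 + 1.53 | 37.8% | 17.4% | 46.4% | 45.5% |

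Exact Fisher power comes from summing over both binomial distributions. At the planned sizes (900/300 and 850/350) it is 86.2% and 89.3% at full capture, 71.8% and 78.1% at 75%, and 15.9% and 21.6% at 25%. With counts this small, the normal formula is optimistic at low capture.

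**Step 4: weight of a single event.** At 613/306, Fisher's p is 0.037 for 0 against 3 events and 0.11 for 0 against 2.

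**Step 5: effect on the estimate.** With equal capture and no false positives, the expected risk ratio is unchanged: (0.02·s)/(0.0013·s) = 15.4 for any s. The loss is of events and power, not a shift in the ratio.

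**The case against.** Several points on the other side have force.

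- **The SPR is a second source.** The bracketed codes follow the National Patient Register, and the text does not say whether they also limit the SPR. SPR tick boxes for thrombosis are not excluded. This stands, so the article does not show that I82 and I26 are the only route to an event. The answer is incomplete, however: the tick-box wording belongs to a different item, no other thrombosis variable is named, and Box 1 says the SPR covers pregnancies only to the visit at 8–12 weeks post partum. The end of the 3-month window may rest on the National Patient Register.
- **The list is headed as examples, in an article that condenses a fuller protocol.** That would excuse giving no codes. The article gives a specific list for a powered outcome, and that list has a gap.
- **The size of the loss is unknown.** This stands. A reader might infer that many events will be missed, but the documents give no share coded outside I82 and I26, and do not say whether I codes are recorded alongside O codes.
- **The Table 3 rates may use the same two codes.** This also stands. If so, the planned power is unaffected.
- **The planned groups exceed 613/306.** This stands too. By the plan's formula, 75% capture at the planned sizes leaves power just under 80%.

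A reader might also infer that infected women, more often cared for outside obstetric wards, receive I codes more often, which would inflate the contrast. Nothing in the documents describes coding by ward or group, so no size can be put on this. It is a reason to report cases by chapter.

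**Conclusion.** The stated code list has a real gap for an outcome sought in pregnancy and the puerperium. Events coded correctly to O22, O87, O88 or I80 would be counted as no event unless the SPR supplies them.

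The consequence for power is conditional on two things: that 0.13% and 2% describe all thromboembolism, and that capture is equal in both groups. Under those assumptions, with capture of 75% to 25%, formula power falls from 80% to 70–38% at 613/306. At the planned sizes it falls from about 85–87% to 77–78% at 75% capture and 45–46% at 25%. If the rates rest on I82 and I26, the power figure holds, but the result cannot be reported as thromboembolism without qualification.

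The documents do not support saying that the outcome rests on these two codes alone or that most events are lost. The study calls itself exploratory, thrombosis is one of five powered outcomes, and the query can still be corrected before register data are extracted. This is a clear correction to make, not a threat to the study as a whole.

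**What to change.** 1. Extend the list under Examples of outcome definition to O22.3, O22.5, O87.1, O87.3, O88.2, I80.1–I80.3, I26, I82 and the I-chapter cerebral venous thrombosis codes, each written out by number. Apply it to the National Patient Register and the SPR over pregnancy and 3 months post partum.
2. State what the SPR contributes: ICD-10 codes, a tick box or both, and up to what time after delivery.
3. Confirm which definition lies behind 0.13% and 2% in Table 3. If it differs from the extended list, restate the rates and the power.
4. Report O-chapter and I-chapter cases separately by group, so that any difference in coding practice can be seen.

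The cost is one revised line, one sentence on the SPR, one on Table 3, and a slightly wider query in a linkage already planned. No recruitment or sampling changes.

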### General statistical methodology

Demographics will be presented as numbers (percentage), medians or means as appropriate by distribution. Comparisons between groups will be analysed by Student’s t-test or Mann-Whitney U-test with means or medians and confidence intervals or IQR, as appropriate according to distribution of the variables. Categorical variables will be compared by χ^2^ test or Fisher’s exact test. Correlations will be analysed by Pearson’s r or Spearman’s r as appropriate by distribution of the variable. Regression analyses, unadjusted and adjusted, will be performed to adjust for known confounding variables. Ten cases per variable at the lowest will be considered appropriate to avoid overfitting of the model.

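### Continuous outcomes are assigned the equal-variance Student's t-test although the groups will be about 1:2.4 to 1:3 (1:5 as recruited), where its intervals depend on equal spread; Welch's test would remove that dependence at no cost.

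*Protocol article*

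**What the plan says.** Under General statistical methodology, continuous comparisons are assigned as follows: "Comparisons between groups will be analysed by Student’s t-test or Mann-Whitney U-test with means or medians and confidence intervals". The choice between the two tests is made "as appropriate according to distribution of the variables". No unequal-variance version of the t-test is named, and unequal spread is not a criterion of choice. Categorical variables go to the χ² or Fisher's exact test. The section adds: "Regression analyses, unadjusted and adjusted, will be performed to adjust for known confounding variables". It does not state the variance estimator.

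Under Examples of outcome definition, the listed outcomes include "gestational age at birth, preterm delivery" and birth weight, so some named outcomes are continuous.

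Under Sample size calculations, the recruitment target reads: "initial sample size for recruitment is set to 200 women in the COVID-19 group and 1000 in the screening group". The same sentence then allows for infections found later among screening women: "with an additional 10%–15% with assumed positive tests in the screening group thus more than 300 COVID-19 cases". Table 3 gives assumed prevalences for five binary outcomes, among them preterm delivery (6% versus 12%) and small for gestational age (10% versus 20%). It gives no standard deviation for any continuous outcome.

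**The concern.** Student's t-test estimates one common variance, and with unequal groups the larger group dominates that estimate. When sizes are close, the resulting standard error is nearly right even if the variances differ. At 1:2.4 to 1:5 it is not. If the smaller group is more variable, the standard error is too small and the interval too short; if it is less variable, the reverse holds.

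The outcomes most exposed are gestational age and birth weight. If infection raises the share of women who deliver early while most still deliver at term, the spread in the COVID-19 group rises along with the shift in mean. At stake is the stated precision of crude mean differences. More recruitment at the same ratio would not cure it, because coverage depends on the size ratio and the variance ratio, not on the total number.

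**Working it through.** **1. The plan's own figure.** "Sample size has been calculated with 80% power and a significance level of <0.05 based on the assumptions shown in table 3". For preterm delivery, with pooled variance under the null, two-sided α of 0.05 and allocation k = 2 screening women per COVID-19 woman:

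n(COVID-19) = [1.96·√((1 + 1/k)·p̄(1 − p̄)) + 0.8416·√(p₁(1 − p₁) + p₀(1 − p₀)/k)]² / (p₁ − p₀)²

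with p̄ = (0.12 + 2 × 0.06)/3 = 0.08. This gives [1.96·√0.1104 + 0.8416·√0.1338]² / 0.0036 = (0.651 + 0.308)²/0.0036 ≈ 255.5, hence 256 and 511 as stated. The other rows reproduce to within one woman in the COVID-19 group. Table 3 is therefore sound as arithmetic, but it rests on proportions only and carries no information on the spread of a continuous outcome.

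**2. Group sizes.** As recruited: 1000/200 = 5. With 10% reclassified: 900/300 = 3. With 15%: 850/350 = 2.43.

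**3. Coverage formula.** Let q be the ratio of standard deviations (COVID-19/screening), n₁ the COVID-19 size and n₀ the screening size. In large samples:

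R = pooled SE / true SE = √{ [(n₁q² + n₀)/(n₁ + n₀)]·(1/n₁ + 1/n₀) / (q²/n₁ + 1/n₀) }, and coverage = 2Φ(1.96·R) − 1.

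Example, q = 1.2 at 200:1000. The pooled variance is (200 × 1.44 + 1000)/1200 = 1.0733. The squared pooled SE is 1.0733 × 0.006 = 0.00644; the true squared SE is 0.0072 + 0.001 = 0.0082. So R = 0.886 and coverage is 91.8%.

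| Assumed q | 200:1000 | 300:900 | 350:850 |
|---|---|---|---|
| 0.9 | 96.5% | 96.1% | 95.9% |
| 1.0 | 95.0% | 95.0% | 95.0% |
| 1.1 | 93.4% | 93.8% | 94.0% |
| 1.2 | 91.8% | 92.7% | 93.1% |
| 1.33 | 89.6% | 91.2% | 91.9% |

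Every q here is an assumption.

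**4. Which q is plausible?** Take a mixture of term and preterm births with 6% versus 12% preterm. The variance at preterm share p is p·s_p² + (1 − p)·s_t² + p(1 − p)(m_t − m_p)². The component values below are assumed.

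- Gestational age (term 39.8, SD 1.3 weeks; preterm 34, SD 2.5 weeks): variances 5.79 and 3.86, ratio 1.50. Coverage is 91.3%, 92.4% and 92.9% at the three sizes.
- Birth weight (term 3550, SD 460 g; preterm 2400, SD 700 g): variances 384,664 and 302,893, ratio 1.27. Coverage is 93.0%, 93.5% and 93.8%.
- Another set of gestational-age components (term mean 280 days, SD 8–10; preterm mean 240–250, SD 8–20) gives q of 1.13–1.25. Coverage is 90.9%–92.9%, 92.1%–93.5% and 92.6%–93.7%.

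**5. Simulation of the first two mixtures** (6000 data sets per setting): Student 91.9%–94.2%, Welch 94.4%–95.4%.

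**6. Price of Welch when variances are equal** (effect 0.2 SD, simulated power): 73.5% Student versus 73.4% Welch at 200:1000; 85.0% versus 84.9% at 300:900.

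**The case against.** A reader might infer that the plan itself assumes a larger spread in the COVID-19 group, so that its intervals must be too narrow. The article does not support that. Table 3 holds prevalences only. Under normality with equal standard deviations, 6% to 12% preterm is a pure shift of 0.38 SD and 10% to 20% small for gestational age a pure shift of 0.44 SD; Student's interval then covers 95%. Small for gestational age is also defined relative to gestational age, so its rate does not fix the variance of birth weight. This objection stands, and the point is therefore conditional.

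A reader might also turn the coverage shortfall into a type I error of 6%–9%. That does not follow. In the mixtures above the means differ too (0.06 × 5.8 = 0.35 weeks; 0.06 × 1150 = 69 g), so rejection is not a false positive. If infection left the preterm rate unchanged, the two mixtures would be identical. What these models show is under-coverage, not inflated false-positive error.

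Further, gestational age is left-skewed, and the distribution rule may send it to Mann-Whitney; the gestational-age figures would then not apply. Nor is there ground to charge the article with calling Mann-Whitney a test of medians: it only reports medians beside it.

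Silence on robust standard errors is a detail that an article may leave to the full protocol or analysis plan. The study is described as exploratory, and confounding is addressed by regression rather than by the crude test. All of this lowers the consequence. It does not give a reason to prefer the equal-variance test, which is a stated choice.

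**Conclusion.** The point holds as a low-severity improvement. The article names an equal-variance test for groups whose sizes give little protection against unequal variances. If the COVID-19 group has the larger spread, as a doubled preterm rate makes plausible without establishing it, nominal 95% intervals for mean differences would cover about 92%–94% at the expected analysis ratios of 1:3 to 1:2.4, and 91%–93% at the recruitment ratio of 1:5. These figures rest on assumed mixture components and apply only to outcomes actually analysed by Student's test. With equal spread there is no error; with smaller spread in the COVID-19 group the intervals are too wide (about 96% at an SD ratio of 0.9). Welch's interval is appropriate in each case. The powered outcomes in Table 3 are binary, go to other tests and are unaffected.

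**What to change.** In General statistical methodology, replace Student's t-test by Welch's unequal-variance t-test, with the matching confidence interval for the difference in means. Where linear regression is used for the same outcomes, state that heteroscedasticity-robust standard errors will be used, so that unadjusted and adjusted estimates rest on the same footing; this may be placed in the analysis plan.

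The cost is one sentence. It needs no additional data and no change in sample size, and the power loss when variances are equal was about 0.1 percentage point in the settings simulated.
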